## Abstract

**Background:**

Convulsive status epilepticus (CSE) is the most common life-threatening neurological emergency in childhood. These children are also at risk of significant morbidity, with acute and chronic impact on the family and the health and social care systems. The current recommended first-choice, second-line treatment in children aged 6 months and above is intravenous phenytoin (fosphenytoin in the USA), although there is a lack of evidence for its use and it is associated with significant side effects. Emerging evidence suggests that intravenous levetiracetam may be effective as a second-line agent for CSE, and fewer adverse effects have been described. This trial therefore aims to determine whether intravenous phenytoin or levetiracetam is more effective, and safer, in treating childhood CSE.

**Methods/design:**

This is a phase IV, multi-centre, parallel group, randomised controlled, open-label trial. Following treatment for CSE with first-line treatment, children with ongoing seizures are randomised to receive either phenytoin (20 mg/kg, maximum 2 g) or levetiracetam (40 mg/kg, maximum 2.5 g) intravenously. The primary outcome measure is the cessation of all visible signs of CSE as determined by the treating clinician. Secondary outcome measures include the need for further anti-seizure medications or rapid sequence induction for ongoing CSE, admission to critical care areas, and serious adverse reactions. Patients are recruited without prior consent, with deferred consent sought at an appropriate time for the family. The primary analysis will be by intention-to-treat. The primary outcome is a time to event outcome and a sample size of 140 participants in each group will have 80% power to detect an increase in CSE cessation rates from 60% to 75%. Our total sample size of 308 randomised and treated participants will allow for 10% loss to follow-up.

**Discussion:**

This clinical trial will determine whether phenytoin or levetiracetam is more effective as an intravenous second-line agent for CSE, and provide evidence for management recommendations. In addition, this trial will also provide data on which of these therapies is safer in this setting.

**Trial registration:**

ISRCTN identifier, ISRCTN22567894. Registered on 27 August 2015

EudraCT identifier, 2014-002188-13. Registered on 21 May 2014

NIHR HTA Grant: 12/127/134

**Electronic supplementary material:**

The online version of this article (doi:10.1186/s13063-017-2010-8) contains supplementary material, which is available to authorized users.

## Background

Convulsive status epilepticus (CSE) is the most common life-threatening neurological emergency in children, with an incidence of 20 per 100,000 children per year [1, 2]. It is the second most common reason for unplanned admission to paediatric intensive care units (PICUs) in the UK, accounting for 5.6% of all PICU admissions [3]. These children are also at increased risk of irreversible morbidity including chronic drug-resistant epilepsy, neurodisability, and learning difficulties, which result in major long-term demands on acute and chronic health and social care resources [4].

The current UK emergency care pathway for the management of childhood CSE is the step-wise algorithm advocated in advanced paediatric life support (APLS) [5]. First-line treatment is two doses of a benzodiazepine given 10 min apart; if the child continues to fit 10 min after the second dose of benzodiazepine, a second-line anticonvulsant is administered. APLS recommends phenytoin as the first-choice second-line anticonvulsant; if the child is allergic to phenytoin, has previously not responded to it, or has experienced a serious adverse event (SAE), phenobarbital is recommended. Failure to stop CSE necessitates rapid sequence induction (RSI), intubation, and admission to the PICU, with consequent potential for iatrogenic consequences including pneumonia, hospital-acquired infections, and prolonged admission.

There is an absence of randomised evidence to support the use of phenytoin as the second-line anticonvulsant despite its use as a standard intravenous (IV) anticonvulsant for the treatment of CSE since the 1940s. A retrospective case note review in which 87% (331/381) children administered a second-line anticonvulsant received phenytoin reported seizure cessation in 190 cases (50%) [6]. There is considerably more literature on phenytoin’s potential adverse effects, including potentially fatal cardiac arrhythmias and Stevens-Johnson syndrome (Table 1) [7–9]. The risk of a cardiac arrhythmia is related to the rate of infusion and phenytoin is therefore infused over at least 20 min.

**Table 1 Tab1:** Comparison of phenytoin and levetiracetam

	Phenytoin	Levetiracetam
Easy to administer^a^	☒	☑
Rapid onset of action^a^	☑	☑
Intermediate to long action^a^	☑	☑
Broad spectrum^a^	☒	☑
Minimal morbidity^a^	☒	☑
Useful as maintenance AED^a^	☑	☑
IV solution compatibility^a^	☒	☑
Rate of infusion	20 min (minimum)	5 min (minimum)
Effectiveness in CSE (seizure termination rate)	50–60%	75–100%
Evidence base		
Cost		
Interactions with other drugs		
Adverse effects		
Potentially fatal	Cardiac arrhythmia Cardiac asystole Stevens-Johnson syndrome	
Non-fatal	Hypotension Hepatotoxicity Phlebitis Severe extravasation injury (‘purple glove syndrome’)	Dizziness Somnolence Headache Agitation IV site irritation

^a^Characteristics of ideal intravenous AEDs as outlined by Wheless and Treiman [41]

*AED* anti-epileptic drug, *CSE* convulsive status epilepticus, *IV* intravenous

Levetiracetam is a broad-spectrum anticonvulsant which effectively treats focal and generalised tonic-clonic and myoclonic seizures. A growing body of evidence, predominantly but not exclusively anecdotal, suggests that IV levetiracetam is safe and effective in the treatment of acute repetitive seizures and both convulsive and non-convulsive status epilepticus, with reported seizure cessation rates between 76 and 100% [10–18]. Both levetiracetam and lorazepam seem to be equally effective in terminating CSE (relative risk 0.97, 95% confidence interval 0.44 to 2.13) [19]. A systematic review published in 2012 indicated that efficacy ranged from 44 to 94% with reported higher rates in retrospective studies [20]. Reported IV levetiracetam doses range from 20 to 60 mg/kg with infrequent and mild adverse effects even at the upper extreme of the dose range [21]. These include dizziness, somnolence, headache, and transient agitation, but there have been no reports of arrhythmias, hypotension, tissue extravasation reactions, Stevens-Johnson syndrome, or hepatotoxicity (Table 1) [21, 22]. Levetiracetam can be infused over 5–7 min, which suggests that, theoretically, CSE may be terminated more rapidly than with phenytoin. Consequently, a reasonable hypothesis is that levetiracetam may be more effective and safer than intravenous phenytoin in terminating CSE [10, 23, 24].

CSE management has been identified as a key priority area for research by a number of sources including the national paediatric emergency medicine research network (Paediatric Emergency Research in the United Kingdom & Ireland; PERUKI) [25] in their inaugural prioritisation exercise [26], and the National Institute for Health and Care Excellence (NICE) in their update of their national epilepsy guideline published in January 2012 [27]. A high-quality randomised controlled trial (RCT) is therefore essential to determine whether phenytoin or levetiracetam is the ideal drug in CSE, as highlighted in the recent systematic review [20].

The EcLiPSE study (Emergency treatment with Levetiracetam or Phenytoin in Status Epilepticus in children) is a phase IV, multi-centre, parallel group, randomised controlled, open-label trial comparing IV levetiracetam with IV phenytoin. The study objectives are to determine which treatment is: 1) more effective as a second-line anticonvulsant for the management of childhood CSE; 2) associated with fewer adverse effects.

## Methods

The protocol for this study has been written in accordance with the Standard Protocol Items: Recommendations for Interventional Trials (SPIRIT) checklist (Additional file 1).

### Study setting

Thirty Emergency Departments (ED) throughout all regions of the UK are participating, selected from the membership of PERUKI, a collaborative paediatric emergency medicine research network [25]. Participating sites may be tertiary or district general hospitals with EDs that treat either children alone, or children and adults. A full list of participating centres is available on the EcLiPSE website (http://www.eclipse-study.org.uk/). Centres are selected based on factors including site research infrastructure, number of likely recruits, and proposed training strategy.

### Study population

#### Inclusion criteria

Children aged 6 months to <18 years who present with generalised tonic-clonic, generalised clonic, or focal clonic CSE that requires second-line treatment, provided that first-line treatment has been administered according to APLS guidelines [5] or the child’s personalised rescue care plan. If patients are given more than two doses of benzodiazepines (for example, in the community and then the ED), or fewer than two doses (for example, due to previous benzodiazepine sensitivity), or where the personalised care plan includes rectal paraldehyde as first-line treatment, then they are still eligible. Children receiving oral phenytoin or levetiracetam as maintenance therapy are eligible.

#### Exclusion criteria

Children are excluded if they: 1) present with absence, myoclonic, or non-convulsive status epilepticus, or infantile spasms; 2) are known or suspected to be pregnant; 3) have a known contraindication or allergy to levetiracetam or phenytoin; 4) have known established renal failure; 5) have been given a second-line antiepileptic drug during this episode of CSE prior to eligibility assessment; or 6) are known to have previously been treated in the EcLiPSE study.

### Outcome measures

The primary outcome is time from randomisation to cessation of all visible signs of CSE activity. The secondary outcomes are: 1) need for further anticonvulsants to manage seizures after randomised treatment; 2) need for RSI due to ongoing CSE; 3) need for admission to a PICU or high-dependency unit (HDU); and 5) serious adverse reactions (SARs) including death, airway complications, cardiovascular instability, extravasation injury, and extreme agitation.

### Screening, randomisation, recruitment, and consent

The overall study flowchart is presented in Fig. 1.

**Fig. 1 Fig1:**
[figure not shown]
Emergency treatment with Levetiracetam or Phenytoin in Status Epilepticus in children (EcLiPSE) study flowchart. *CSE* convulsive status epilepticus

#### Screening

Screening commences once a child arrives in the ED and has received first-line treatment for CSE. A unique participant screening form is used which includes an eligibility assessment and reasons for non-randomisation where appropriate.

#### Randomisation and recruitment

Eligible children are randomised following completion of first-line therapy if the CSE is ongoing, enabling preparation and administration of the allocated treatment in a timeframe consistent with APLS guidance [5]. If the CSE terminates prior to administration of the allocated treatment then the patient may still be given that treatment if the CSE restarts while they remain in the ED. Randomised participants who do not receive a second-line treatment in the ED will not be included in the primary outcome analysis.

Screening data from randomised participants who do not receive a second-line treatment in the ED will be collected and analysed in conjunction with randomised and treated participants.

Participants are randomised to levetiracetam or phenytoin in a ratio of 1:1 (Fig. 2), and the randomisation code list is generated by an independent statistician. Randomisation packs are sequentially numbered opaque tamperproof envelopes, to be opened in ascending order. Checks are performed periodically to ensure the correct number of randomisation packs is present, that they are intact, and that the sequential numbering system is maintained. The envelopes contain the first case report form (CRF) which is completed in the ED during the CSE episode. Data collected include time of drug administration, CSE cessation, additional therapy required, adverse events, and admission location.

**Fig. 2 Fig2:**
[figure not shown]
Schematic of Emergency treatment with Levetiracetam or Phenytoin in Status Epilepticus in children (EcLiPSE) study design. ^1^Administration of the first-line treatment may have occurred prior to arrival in the ED. ^2^If a patient is randomised but *not* treated with a second-line anticonvulsant, follow-up would end at this point. *APLS* advanced paediatric life support, *CRF* case report form, *ED* Emergency Department

### Follow-up

There are three time-periods for data collection in the EcLiPSE study (Figs. 1, 2, and 3). The first is in the ED during the acute CSE treatment phase. The second is the 24 h after allocated treatment, wherein data collected include further seizures, concomitant anticonvulsants that may have been required to treat other acute seizures, and adverse events. Finally, safety follow-up is undertaken 14 days after administration of the randomised treatment by review of hospital notes and a single-sheet, four-question questionnaire completed by the child’s parents. This includes information on whether there have been further admissions or organ failure.

**Fig. 3 Fig3:**
[figure not shown]
Emergency treatment with Levetiracetam or Phenytoin in Status Epilepticus in children (EcLiPSE) study assessments. *This physical examination should include a comment on any focal neurological signs. *CRF* case report form, *X* as indicated/appropriate

### Blood samples

Samples are taken 1–2 h after completion of the randomised treatment to measure drug levels, a common practice when giving phenytoin [28]. Levetiracetam levels are measured in an accredited central laboratory, to which samples are not transferred until study consent has been obtained. Measurement of phenytoin levels is undertaken in the treating hospital.

### Trial treatments

EcLiPSE is an open-label trial using investigational medicinal products (IMPs) with marketing authorisation in the UK. These only become IMPs when the packaging is opened in the setting of this study. IMP provision is the responsibility of each site in accordance with standard clinical practice, and they are stored in line with local requirements for general medicine supplies.

A single dose of the randomly allocated treatment is administered by IV infusion. The levetiracetam dose is 40 mg/kg (maximum 2500 mg) over 5 min, diluted to a maximum of 50 mg/ml with 0.9% sodium chloride. The phenytoin dose is 20 mg/kg (maximum dose 2000 mg) at a rate not exceeding 1 mg/kg/min (or longer than 20 min for doses of >1 g), diluted with 0.9% sodium chloride to a maximum concentration of 10 mg/ml.

The allocated treatment is prepared and administered in accordance with standard clinical care with independent checking performed by two trained personnel. Trial-specific labelling is not required; rather, an approved “intravenous additive label” is used. If the randomised treatment is discontinued prior to administration of the full dose this is recorded. If CSE persists at the end of the IMP infusion, further medical management is decided by the local clinical team independent of the trial protocol (Fig. 2).

### Consent study

EcLiPSE includes a mixed method study (consent study) involving participants and trial recruiters to explore: 1) how information about the trial and deferred consent is exchanged during recruitment discussions; 2) views on deferred consent and participant decision making; 3) the impact of an un-blinded trial design; and 4) trial recruiter training [29–31]. The objective of the consent study is to identify potential barriers and solutions to recruitment and consent. This will inform recruiter training both during EcLiPSE and also inform approaches to recruitment and consent for future paediatric critical care trials. The consent study involves the following.

#### Audio-recording of recruitment and consent discussions between families and trial recruiters

EcLiPSE recruiters seek verbal permission to audio-record recruitment consultations when they first approach families about EcLiPSE; if permission is declined the recruitment consultation is not recorded. If there is more than one trial discussion, then all are recorded. Audio-recording occurs for the first 4 months of the trial at each site, or until data saturation is achieved [32].

#### Questionnaires completed by participant representatives after EcLiPSE consent discussions

EcLiPSE trial recruiters will invite all participants (including those who decline deferred consent) to complete an online or paper consent study questionnaire. If more than one participant is involved in the consent discussion, then all are invited to complete a questionnaire.

#### Telephone interviews with up to 25 parents of patients, 16- to 18-year-old patients with capacity, and one member of each site team

EcLiPSE recruiters ask participants who agree or decline consent if they wish to take part in a telephone interview. If they agree, the consent study researcher contacts them to arrange interviews within 1 month of the discussion. Interviews are likely to be conducted until data saturation is reached [32]. One member of each site team (Principal Investigator (PI) or research nurse) is emailed by the consent study researcher asking them to participate in a telephone interview within the first 4 months of site opening

#### Focus groups with EcLiPSE trial recruiters

At the end of the first year, the consent study researcher will invite EcLiPSE staff in 6–10 sites to participate in a focus group. Selection of sites for focus groups will be based on recruitment rates (both high and low) and recruitment issues identified in the analysis of audio-recordings, questionnaires, and parent interviews

Table 2 summarises when each section of the consent study is applicable to participants who have been randomised and administered treatment. Participants can select which study elements they wish to take part in during the consent process.

**Table 2 Tab2:** Consent study applicability

Consent sought from	Location deferred consent sought	Applicable sections of the consent study		
		Audio-recording	Questionnaire	Interview
Parent/legal representative	On-site	✓	✓	✓
Bereaved parent/legal representative	On-site			✓
Adult with capacity	On-site	✓		✓
Parent/legal representative	Home		✓	✓
Bereaved parent/legal representative	Home			✓
Adult with capacity	Home			✓

### Statistical considerations

A separate and full statistical analysis plan will be developed prior to the final analysis of the trial and agreed by the Trial Steering Committee (TSC).

#### Sample size estimation

Sample size estimation is based on published seizure cessation rates for phenytoin (50–60%) [6] and levetiracetam (76–100%) [10–18, 22, 23]. A sample size of 140 participants in each group at a 0.05-level two-sided log-rank test for equality of survival curves will have 80% power to detect an increase in seizure cessation rates from 60% to 75%, (a constant hazard ratio of 0.661). A total of 308 randomised participants with deferred consent and given randomised treatment will allow for 10% loss to follow-up.

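### The total of 308 covers 9.1% loss to follow-up, not the stated 10%; the effect on power is negligible

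*Protocol article*

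**What the plan says.** The sample size estimation section of the protocol article bases the size on a "0.05-level two-sided log-rank test for equality of survival curves", with 80% power for cessation rates of 60% against 75%, expressed as "a constant hazard ratio of 0.661". The requirement is "A sample size of 140 participants in each group", so 280 in total under 1:1 allocation. The section then adds the allowance: "A total of 308 randomised participants with deferred consent and given randomised treatment will allow for 10% loss to follow-up".

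The methods paragraph of the abstract repeats the 140 per group and gives the allowance as: "Our total sample size of 308 randomised and treated participants will allow for 10% loss to follow-up". It agrees with the sample size section on 308, on 10% and on treatment having been given. It does not repeat the condition that deferred consent was obtained.

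**The concern.** An allowance for loss is meant to leave the required number once the loss has happened. If a proportion d is lost from N recruited, N(1 - d) must reach the requirement, so N is the requirement divided by (1 - d). Adding 10% of the requirement instead gives a total that is slightly too small, because the 10% is later lost from the larger number. The stated 308 is exactly the result of that addition.

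Little is at stake. The sentence describes a property of the design that the number does not have, and it appears twice, so it is likely to be carried into the trial report. The question is whether the slip also damages the stated power.

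**Working it through.** **Inputs, all from the sample size estimation section unless noted:** two-sided alpha 0.05; power 80%; cessation 60% and 75% (mean 0.675); hazard ratio 0.661; 140 per group; loss 10%; stated total 308. The 1:1 allocation is from the section on randomisation and recruitment.

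**1. Reproducing the base size.**
- Hazard ratio: ln(0.40)/ln(0.25) = 0.661, as stated.
- Freedman events: 7.849 x [(1 + 0.661)/(1 - 0.661)]² = 7.849 x (1.661/0.339)² = 188.4, where 7.849 is the squared sum of the normal quantiles for two-sided 0.05 and 80% power.
- Children: 188.4/0.675 = 279.2, or 139.6 per group, rounded up to 140.

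The stated 140 per group reproduces. Schoenfeld's formula gives 183.2 events, 271.4 children and 136 per group, so 140 matches Freedman, although the article does not name the formula.

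**2. Reproducing 308.**
- 280 x 1.10 = 308.0 exactly.
- 280/0.90 = 311.1, or 312 in equal groups (156 each).
- Difference: 312 - 308 = 4 children; 4/312 = 1.3%.

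**3. What 308 covers.**
- Largest loss that still leaves 280: 1 - 280/308 = 9.1%.
- After 10% loss: 308 x 0.90 = 277.2, about 3 short of 280.

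**4. Effect on power.** Expected events are 0.675 times the number analysed, and a lost child is assumed to contribute nothing. Freedman power is Φ(√events x 0.339/1.661 - 1.96). Schoenfeld power is Φ(√events x |ln 0.661|/2 - 1.96).

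| Analysed | Events | Freedman | Schoenfeld |
|---|---|---|---|
| 280 (requirement) | 189.0 | 80.1% | 81.2% |
| 277.2 (308 less 10%) | 187.1 | 79.7% | 80.8% |
| 280.8 (312 less 10%) | 189.5 | 80.2% | 81.3% |

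Moving from 280 to 277 analysed costs about 0.4 percentage points under either formula.

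**The case against.** The strongest reply is that nothing of substance changes. Power of 79.7% rounds to the 80% claimed. Under Schoenfeld's formula the unrounded requirement is 271.4, and 271.4/0.90 = 301.5, so 308 would more than cover 10% loss. Adding 10% of the requirement is also a common convention. In addition, the outcome is a time to event analysed by the log-rank test, and cessation is recorded in the emergency department during the episode. A child with incomplete follow-up may be censored and still contribute time at risk, so even the 0.4-point drop is towards the upper end.

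All of this stands as a statement about size, and it rules out any claim that the trial is underpowered. It does not rescue the sentence. The article sets its own requirement at 140 per group, and 10% loss from 308 does not leave 280, whichever formula lies behind the 140.

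A reader might also infer a stronger point from the two descriptions of the 308: that the abstract counts treated children without consent, that where recruitment stops depends on which sentence is followed, and that children without consent would erode the 308 and the power further. The document does not support this. The sample size section defines the 308 in full as randomised, with deferred consent and treated. The abstract is a condensed statement that drops one qualifier, and the same paragraph says that deferred consent is sought. Nothing suggests that recruitment would be closed on the abstract's count. The article gives no rate of non-consent, so any loss of power from that source would rest on invented figures.

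**Conclusion.** The point holds as an error in the stated allowance. The 308 was obtained as 280 x 1.10 and covers 9.1% loss, not 10%. At 10% loss, 277 of the required 280 remain. Power is then about 79.7% by Freedman's formula or 80.8% by Schoenfeld's, so the design is not materially affected.

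The arithmetic on 308 rests only on figures in the article. The power figures assume the stated cessation rates, a constant hazard ratio of 0.661, and no information from children lost to follow-up. The missing consent qualifier in the abstract is a matter of consistent wording, with no demonstrated effect on recruitment or power.

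**What to change.** In both the abstract and the sample size section, say that 308 allows for about 9% loss to follow-up, with about 79.7% power at 10% loss. If the 10% allowance is to be kept as stated, the matching total is 312, which is 4 more children. In the abstract, add the deferred-consent qualifier so that the 308 is described as it is in the sample size section.

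The cost is one sentence in two places. Restating the allowance needs no extra patients and changes no analysis.
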